#### Statistical analysis

All variables will be analyzed using descriptive statistics (frequency, mean ± standard deviation [SD], range or median ± interquartile range, whichever is appropriate). Student’s t-test will be used to compare mean values. A Chi-square test will be used to compare frequencies and proportions in two or more groups. Data will be used for a nested case–control study comparing patients with and without SDB (analysis population I) or patients with different severity and type of SDB (analysis populations II and III) with respect to their characteristics and history. Multivariate logistic regression modelling will be used to analyze the associations between suspected causes of SDB and the risk of developing that disorder taking the cluster structure of the data entered by the recruiting cardiologists into account. The models will include potential clinical predictors of SDB, or of the extent of SDB, that are assessed in the SchlaHF registry such as age, BMI, gender, LVEF, NYHA class, aetiology of HF, and atrial fibrillation. Models will be fitted by likelihood ratio-based stepwise backward variable selection. The predictive accuracy of the resulting models will be judged by cross validation. A p value of <0.05 is considered to be statistically significant. Statistical analysis will be performed with SPSS version 19.0 or higher (SPSS Inc., Chicago, USA) or STATA 12.0 or higher (StataCorp LP, College Station, Texas, USA).

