## Background

The prevalence of heart failure (HF) in western countries is about 1-2% of the adult population, with significant increases as age increases [1,2]. Recent guidelines differentiate between HF due to reduced systolic left ventricular ejection fraction (HF-REF) and HF with preserved ejection fraction (HF-PEF) and impaired diastolic function [3]. HF-REF is the most widely investigated and best understood type of HF [3], with a high prevalence in males with ischemic heart disease. In contrast, HF-PEF is more prevalent in women and often has a non-ischemic aetiology. Epidemiological data suggest that HF-REF and HF-PEF have a similar prognostic impact [4].

A number of co-morbidities have been linked to the development and progression of HF. One that is gaining increasing recognition is sleep-disordered breathing (SDB) with predominant obstructive (OSA) or central sleep apnea (CSA) with or without Cheyne-Stokes respiration (CSR). Small studies published to date have reported that the prevalence of SDB was almost 70-80% in patients with HF-PEF and up to 76% in those with HF-REF based on a cut-off of an apnea-hypopnea index (apneas and hypoponeas per hour of recording time; AHI) ≥ 5/h while moderate to severe sleep apnea with an AHI ≥ 15/h was prevalent in about half of the patients [5-7].

The Sleep Heart Health Study identified OSA as an independent risk factor for the development of HF [8], with more impact in men than in women [9]. Patients with CSA have been shown to have a reduced quality of life [10] and to be at increased risk of developing cardiac arrhythmias [11]. In addition, the prevalence of CSA-CSR appears to increase as the severity of HF increases and cardiac function decreases [5,6]. Thus, the occurrence of CSA-CSR and its severity is thought to mirror cardiac dysfunction [12,13]. In addition, SDB in general [14], as well as OSA [15] and, in particular, CSA [16,17] have been shown to be independently associated with worse prognosis in patients with HF-REF. Even when HF-REF patients are receiving optimal treatment of HF, including cardiac resynchronization therapy (CRT), even a low level of CSA-CSR or OSA appears to have a major impact on prognosis [18].

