## Discussion

Data from both large-scale clinical trials and registries have provided a large volume of data on patients with cardiovascular disease. It is increasingly recognised that large randomised, controlled clinical trials are extremely expensive to perform and often generate results that may not be generalizable to a wide population of patients in clinical practice [33]. Thus, the combination of good quality clinical studies and prospective registries is likely to be the best approach to identifying, defining and applying treatments and strategies to improve patient outcomes [19].

The focus of the SCHLA-HF registry is SDB in patients with HF-REF. SDB is increasingly being recognised as an independent risk factor for the development of HF [8,9,14,34,35] and as making an important contribution to worse outcomes in these patients [14-16]. In addition, worsening HF appears to increase the incidence and severity of SDB [5,6], while effective treatment of SDB appears to improve clinical outcomes in patients with HF [14,36].

One multicenter study and 5 single-center studies with ≥100 participants provide estimates of SDB prevalence in HF-REF (Table 1) [6,37-42]. Previous studies consistently indicate that the SDB is very common in HF. However, the SCHLA-HF registry may overcome some limitations of the previous studies. This will be achieved in a number of ways. Firstly, by including HF-REF patients from a large number of cardiology practices or hospital cardiology departments, the SCHLA-HF-registry will study a more representative sample compared to studies from specialized hospital cardiology departments [6,38,40,41] or sleep clinic populations [39] alone. Secondly, since the proportion of women with both HF-REF and SDB was low in previous studies, a very high total sample size, as targeted in the SCHLA-HF registry, is required to provide robust analyses of SDB prevalence and risk factors in women. Finally, in contrast to some of the previous studies [38-40], patients of the SCHLA-HF registry will be on current medical therapy for HF-REF.

**Table 1 T1:** Prevalence of sleep-disordered breathing in chronic heart failure

**Study**	**Setting**	**Total patients (n)**	**Females (n)**	**SDB (AHI ≥15/h)**	**ß-blocker**	**Spironolactone**
Schulz et al. 2007 [37]	Multicenter	203	51	-*	90%	46%
Javaheri et al. 2006 [38]	Single center	100	0	49%	10%	0%
Oldenburg et al. 2007 [6]	Single center	700	139	51%	85%	62%

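### Student's t-test is the only test named for means, so its error rate can leave 5% where groups differ in both size and spread, and clustering is handled only in the logistic models

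*Protocol article*

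**What the plan says.** The Statistical analysis section gives one test for means: "Student’s t-test will be used to compare mean values". The next sentence deals with categorical data: "A Chi-square test will be used to compare frequencies and proportions in two or more groups". One threshold applies throughout: "A p value of <0.05 is considered to be statistically significant".

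The comparisons listed are "comparing patients with and without SDB (analysis population I" and "patients with different severity and type of SDB (analysis populations II and III". Gender differences are an objective in the Background, and gender is a candidate predictor in the logistic models.

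The multivariable logistic models are to be fitted "taking the cluster structure of the data entered by the recruiting cardiologists into account". The t-test and chi-square sentences in the same paragraph carry no such provision.

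**The concern.** Student's t-test, in the usual meaning of the name, pools the two groups' variances. If the smaller group has the larger SD, the pooled standard error is too small and the test rejects too often. If the smaller group has the smaller SD, the test rejects too rarely. A large sample protects against non-normal data but not against this, because the ratio of pooled to true variance depends only on the group shares and the SD ratio. At stake is whether p-values for means in unbalanced comparisons mean what the 0.05 threshold implies.

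The second part is independence. The plan recognises that patients are grouped by recruiting cardiologist, but uses this only in the regression models. Prevalence is the registry's first objective, and an interval for it that treats patients as independent would be too narrow if prevalence varies between centres.

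**Working it through.** The plan has no figure of its own to reproduce: the Sample size section states that no formal calculation was done, and no SD is given for any variable. The only stated figure is the nominal 0.05, taken here as two-sided.

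**Inputs from the article**
- Share of women, Table 1: (51 + 0 + 139 + 68 + 50 + 55 + 26) / (203 + 100 + 700 + 450 + 218 + 316 + 176) = 389/2163 = 18.0%. Leaving out the study with no women gives 389/2063 = 18.9%; single studies then range from 14.8% to 25.1%.
- Share with SDB at an apnea-hypopnea index of at least 15/h: the Background says "moderate to severe sleep apnea with an AHI ≥ 15/h was prevalent in about half of the patients"; Table 1 gives 47% to 61%.
- Centres: 138 (Design of the registry).

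**Assumptions, not in the article**
- SD ratios of 0.7 to 1.5.
- 8,000 patients in total, and an intracluster correlation (ICC) of 0.02 to 0.05.

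**Formula for the t-test.** Let one group have share f and SD r, and the other share 1 − f and SD 1. For large N, the pooled variance estimate divided by the true variance of the mean difference is

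k = (f r² + 1 − f) / ((1 − f) r² + f), and the actual type I error is 2[1 − Φ(1.96 √k)].

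**Women against men, f = 0.18**
- r = 0.7: k = 0.908/0.582 = 1.561; 1.96 × 1.249 = 2.449; error 1.4%.
- r = 1.25: k = 1.101/1.461 = 0.754; 1.96 × 0.868 = 1.70; error 8.9%.
- r = 1.5: k = 1.225/2.025 = 0.605; 1.96 × 0.778 = 1.52; error 12.7%.

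**With against without SDB**
- f = 0.50: k = 1 for every r, so the error is 5.0%.
- f = 0.47: 4.7% at r = 0.8 and 5.3% at r = 1.25.
- f = 0.61: 6.2% at r = 0.8 and 4.0% at r = 1.25.

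**Does it shrink with N?** In simulations with normal, independent data (200,000 replicates, f = 0.20, r = 1.25), the pooled test rejected in 8.7%, 8.6% and 8.6% of replicates at N = 200, 2,395 and 10,000. Welch's test stayed between 4.9% and 5.1% in every scenario tried.

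**Clustering**
- Average cluster: 8,000/138 = 58 patients.
- Design effect for a prevalence = 1 + (58 − 1) × ICC: 2.14 at 0.02 and 3.85 at 0.05.
- Standard error of a 50% prevalence, patients independent: √(0.25/8,000) = 0.56 points.
- With clustering: 0.56 × √2.14 = 0.82 and 0.56 × √3.85 = 1.10 points.

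A contrast between patients of the same centre is different, because the centre effect largely cancels; there the design effect is put at only about 1.02 to 1.14.

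**The case against.** The strongest reply is that the problem is hypothetical for the comparison named first. The article's own prevalence figures make the groups with and without SDB nearly equal in size, and equal sizes protect the pooled test whatever the SDs. This stands.

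The article also reports no SDs, so unequal spread is nowhere documented. A reader might infer that the groups are known to differ in size and spread and that the error rate is therefore wrong. The documents do not support that: every SD ratio above is assumed. It is also tempting to argue that the apnea-hypopnea index varies more where it is high. But that index defines SDB, whereas the listed comparisons concern patients' characteristics and history, and the article gives no reason why age, body mass index or ejection fraction should differ in spread.

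Women against men is not among the comparisons listed in the Statistical analysis section. It remains relevant because gender differences are an objective and the Discussion itself gives the imbalance as a reason for a large sample: "since the proportion of women with both HF-REF and SDB was low in previous studies".

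On more than two groups, the article does not say that a t-test will be applied to several groups at once. Not naming an analysis of variance may simply reflect condensation and is not a fault here.

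On clustering, the predictor question is answered by models that allow for it, and within-centre contrasts are barely affected. A reader might infer that all the unadjusted tests are badly distorted; the working does not bear that out. The article does not describe how the prevalence interval will be computed, so an interval that is too narrow is a risk, not a stated error.

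**Conclusion.** The point holds conditionally and is of low priority. The plan fixes the pooled test for all means, and that test loses its nominal 5% level when size and spread both differ, by an amount that does not fade with N. In a split of 18% to 82% the error would run from 1.4% to 12.7% over assumed SD ratios of 0.7 to 1.5. For SDB against no SDB it stays at about 4% to 6% over ratios of 0.8 to 1.25. The exposure is therefore in gender contrasts and in unbalanced subgroups by type or severity of SDB, whose sizes the text does not give.

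Clustering matters mainly for the prevalence estimate and for contrasts between centres. There the standard error could be 1.5 to 2 times the independent-patient value (0.82/0.56 to 1.10/0.56). That rests on the assumed 8,000 patients and ICC of 0.02 to 0.05, and on treating the centre as the cluster.

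Neither part touches the main predictor analysis, which is a cluster-adjusted logistic regression. The affected tests are secondary and univariable.

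**What to change.** Make two separate changes, since neither does the work of the other: Welch's test ignores clustering.

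1. Replace Student's t-test with Welch's t-test, and name Welch ANOVA for three or more groups.
2. Compute the confidence interval for prevalence, and any contrast between centres or centre types, with standard errors clustered on the recruiting centre, in line with the logistic models.

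This costs a sentence or two in the analysis plan and needs no new data. P-values can move either way: they rise where the smaller group has the larger SD and fall where it has the smaller one. The prevalence interval may widen. Where group sizes or SDs are nearly equal, Welch's test gives almost the same result as Student's, so little is lost.

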### Ethics and monitoring

The registry was approved by the local ethics committees of the participating institutions and is being managed in accordance with Good Clinical Practice and the Declaration of Helsinki. All patients provide written informed consent to be included in the registry. The patients are advised in the consent forms that they have the right to withdraw from the registry at any time without it impacting on their treatment. In the event that a patient drops out of the registry, a Registry Termination Form has to be completed, which details the date of termination and reason for termination. The patient is also informed she/he must specifically request that her/his data will not be analysed. Otherwise data remain in the database and will be included in the analysis. Reasonable effort will be made to contact any patient lost to follow-up (between SDB-screening and PSG) in order to complete assessments and retrieve any outstanding data.

## Discussion

Data from both large-scale clinical trials and registries have provided a large volume of data on patients with cardiovascular disease. It is increasingly recognised that large randomised, controlled clinical trials are extremely expensive to perform and often generate results that may not be generalizable to a wide population of patients in clinical practice [33]. Thus, the combination of good quality clinical studies and prospective registries is likely to be the best approach to identifying, defining and applying treatments and strategies to improve patient outcomes [19].

The focus of the SCHLA-HF registry is SDB in patients with HF-REF. SDB is increasingly being recognised as an independent risk factor for the development of HF [8,9,14,34,35] and as making an important contribution to worse outcomes in these patients [14-16]. In addition, worsening HF appears to increase the incidence and severity of SDB [5,6], while effective treatment of SDB appears to improve clinical outcomes in patients with HF [14,36].

One multicenter study and 5 single-center studies with ≥100 participants provide estimates of SDB prevalence in HF-REF (Table 1) [6,37-42]. Previous studies consistently indicate that the SDB is very common in HF. However, the SCHLA-HF registry may overcome some limitations of the previous studies. This will be achieved in a number of ways. Firstly, by including HF-REF patients from a large number of cardiology practices or hospital cardiology departments, the SCHLA-HF-registry will study a more representative sample compared to studies from specialized hospital cardiology departments [6,38,40,41] or sleep clinic populations [39] alone. Secondly, since the proportion of women with both HF-REF and SDB was low in previous studies, a very high total sample size, as targeted in the SCHLA-HF registry, is required to provide robust analyses of SDB prevalence and risk factors in women. Finally, in contrast to some of the previous studies [38-40], patients of the SCHLA-HF registry will be on current medical therapy for HF-REF.

**Table 1 T1:** Prevalence of sleep-disordered breathing in chronic heart failure

**Study**	**Setting**	**Total patients (n)**	**Females (n)**	**SDB (AHI ≥15/h)**	**ß-blocker**	**Spironolactone**
Schulz et al. 2007 [37]	Multicenter	203	51	-*	90%	46%
Javaheri et al. 2006 [38]	Single center	100	0	49%	10%	0%
Oldenburg et al. 2007 [6]	Single center	700	139	51%	85%	62%
Sin et al. 1999 [39]	Single center	450	68	61%	0%	0%
Yumino et al. 2009 [40]	Single center	218	50	47%	75%	21%
Paulino et al. 2009 [41]	Single center	316	55	-*	82%	58%
Dolliner et al. 2013 [42]	Single center	176	26	50%	90%	60%

*reported prevalence of sleep-disordered breathing (SDB) based on a definition using apnea-hypopnea index cixAHI ≥10/h**.**

### Limitations

A multi-step procedure was established to improve the representativeness of the registry and, in particular, to capture as many SDB patients as possible, even if they were not accurately diagnosed at their first visit. However, such a multi-step procedure can itself be a source of bias. Perhaps the most important potential limitation of this study is the interaction/collaboration between cardiology physicians and the sleep laboratories. Such interactions have the potential to introduce bias, and missing PSG results need to be taken into account when interpreting the data.

### Perspective

Effective management of SDB and associated improvements in HF morbidity and mortality is a potential approach to managing the many HF patients who remain symptomatic and have disease progression despite guideline-driven pharmacological and device-based therapy. It is hoped that data gathered by the SCHLA-HF registry will make a substantial contribution to the body of knowledge in the area of HF-REF and SDB. In addition, it has the potential to generate rational hypotheses with respect to the sequence of symptoms, and the aetiology and potential treatment of the disease to be tested in future randomised clinical trials, which have been called for to develop quality treatment guidelines [43]. Hopefully this will lead to better strategies to manage HF, particularly with respect to effective treatment of SDB, which in turn will contribute to improved morbidity and mortality outcomes in these patients.

## Conclusions

Registries play an important role in facilitating advances in the understanding and management of cardiovascular disease. The SCHLA-HF registry will provide consistent data on a large group of patients with HF-REF that will demonstrate aspects of the natural course of the disease and help to answer questions on the prevalence, risk factors, gender differences and stability of SDB in these patients.

## Abbreviations

AHI: Apnea-hypopnea index; ASV: Adaptive servo-ventilation; BMI: Body mass index; CRT: Cardiac resychronization therapy; CSA: Central sleep apnea; CSR: Cheyne-Stokes respiration; HF: Heart failure; HF-REF: Heart failure with reduced systolic function; HF-PEF: Heart failure with preserved ejection fraction; LVEF: Left ventricular ejection fraction; NYHA: New York Heart Association; OSA: Obstructive sleep apnea; PAP: Positive airway pressure; PSG: Polysomnography; SDB: Sleep-disordered breathing.
